## Abstract

**Background:**

Due to improved treatments and ageing population, many countries now report increasing prevalence in rates of ischemic heart disease and heart failure. Cardiac rehabilitation has potential to reduce morbidity and mortality, but not all patients complete. In light of favourable effects of cardiac rehabilitation it is important to develop patient education methods which can enhance adherence to this effective program. The LC-REHAB study aims to compare the effect of a new patient education strategy in cardiac rehabilitation called ‘learning and coping’ to that of standard care. Further, this paper aims to describe the theoretical basis and details of this intervention.

**Methods/design:**

Open parallel randomised controlled trial conducted in three hospital units in Denmark among patients recently discharged with ischemic heart disease or heart failure. Patients are allocated to either the intervention group with learning and coping strategies incorporated into standard care in cardiac rehabilitation or the control group who receive the usual cardiac rehabilitation program. Learning and coping consists of two individual clarifying interviews, participation of experienced patients as educators together with health professionals and theory based, situated and inductive teaching. Usual care in cardiac rehabilitation is characterised by a structured deductive teaching style with use of identical pre-written slides in all hospital units. In both groups, cardiac rehabilitation consists of training three times a week and education once a week over eight weeks. The primary outcomes are adherence to cardiac rehabilitation, morbidity and mortality, while secondary outcomes are quality of life (SF-12, Health education impact questionnaire and Major Depression Inventory) and lifestyle and risk factors (Body Mass Index, waist circumference, blood pressure, exercise work capacity, lipid profile and DXA-scan). Data collection occurs four times; at baseline, at immediate completion of cardiac rehabilitation, and at three months and three years after the finished program.

**Discussion:**

It is expected that learning and coping incorporated in cardiac rehabilitation will improve adherence in cardiac rehabilitation and may decrease morbidity and mortality. By describing learning and coping strategies the study aims to provide knowledge that can contribute to an increased transparency in patient education in cardiac rehabilitation.

**Trial registration:**

Identifier NCT01668394.

## Background

Ischemic heart disease (IHD) and heart failure (HF) are among the leading causes of death in Europe. Further, these diseases cause chronic morbidity and reduced quality of life for around 300.000 patients in Denmark [1]. In recent decades the incidence of IHD has decreased while that of HF has stabilised. However, the prevalence of both has increased due to better treatments and a changing age composition of the population [2, 3].

Cardiac rehabilitation (CR) is thus of great significance due to its known potential to reduce morbidity and mortality, to improve quality of life and affect risk and lifestyle profiles in a positive direction [4–8]. CR was defined by WHO in 1993 as: *“the sum of activities required to influence favourably the underlying cause of the disease, as well as to ensure the patients the best possible physical, mental and social conditions so that they may by their own efforts preserve, or resume when lost, as normal a place as possible in the life of the community”*
[9]. A broader definition of rehabilitation from the World Report on Disability in 2011 is: *“a set of measures that assist individuals who experience, or are likely to experience, disability to achieve and maintain optimal functioning in interaction with their environments”*
[10]. This broader definition includes the patient’s environment such as their family and friends, where they live, and their workplace as essential factors in rehabilitation, thereby emphasising the global perspective of the term.

Many patients with IHD and HF do not succeed with lasting lifestyle improvements and only a fraction of the relevant patient group complete CR [2]. In light of the favourable effects of CR it is important to develop patient education strategies which can help patients to improve adherence to CR and make changes towards a healthier lifestyle [11, 12].

While patient education has been variously defined and implemented in different chronic disease management programs, only limited evidence has been found for its effectiveness on adherence to CR and adherence to lifestyle change. Furthermore, insight about optimal content is lacking in many patient education programs and large, high-quality studies with a long term perspective are required [13]. Reviews of patient education in CR suggest interventions such as self-monitoring of activity, action planning, use of lay volunteers and tailored counselling by CR staff to promote adherence are likely to be successful. However, data is limited and further research is needed on interventions targeting patient-identified barriers to be able to make practice recommendations for increasing adherence to CR [14, 15].

A patient education strategy called ‘learning and coping’ (LC) was developed in Norway to address some of these challenges in patient education. LC is a health pedagogical strategy that builds on situated and inductive teaching with high involvement from the participants [16]. Characteristics of LC are that ‘experienced patients’ plan, teach and evaluate, together with health professionals. LC was implemented as a pilot project in group based patient education for patients with diabetes and chronic obstructive lung disease in the municipalities of the western part of Central Denmark Region. In this pilot project an extra dimension was included in the Danish adaptation of LC, namely that group based programs began and finished with individual ‘clarifying’ interviews [17].

A study, referred to as LC-REHAB, was designed to address the limitations of the available research on patient education in CR. The study evaluates the effectiveness of LC incorporated in CR on adherence, morbidity and mortality, quality of life plus lifestyle and risk factors in a parallel group open randomised design. Beyond presenting the LC-REHAB study protocol the aim of this paper is to also describe the theoretical basis and details of the LC strategies.

## Methods/Design

### Design

LC-REHAB was launched in three hospital units in Regional Hospital West Jutland (RHWJ), Denmark as an open randomised parallel group controlled study within which participants are allocated to either the intervention arm (LC strategies incorporated in standard CR) or to the control arm (standard CR). The randomisation is computer generated in a 1:1 ratio stratified for hospital unit, diagnosis (IHD or HF) and gender, alternating in blocks of two to four. According to power calculations, a total of 750 patients were needed to be recruited for the primary analysis. For secondary analysis of body compositions with Dual energy X-ray absorptiometry (DXA) scans, n = 150 patients were needed.

The CR program in both the intervention and control arms lasts for eight weeks, with training sessions three times a week and one education session per week. All sessions last 1.5 hours. In total, there are 24 training sessions and eight education sessions. The education in both arms is divided into eight topics; one topic per week. The topics are: function and symptoms of the heart, lifestyle effects on the development of IHD and HF, emotional reactions, medication, tiredness, the importance of relatives or other networks, importance and types of exercise, and future life with a chronic disease. The topics were elected on a theme day by LC educated health professionals and experienced patients with ‘The Disease Management Program for cardiovascular disease’ from Central Denmark Region as a general framework [18]. The training sessions are conducted by a physiotherapist in the presence of a nurse in case patients become unwell. The sessions consist of both cardio-stress and muscle-strengthening exercises. The education sessions are presented mainly by a nurse except for the topics on exercise and future life which are presented by the physiotherapist. In each arm of the study, patients are supported by the same team of nurse and physiotherapist throughout the eight week period.

Data is collected four times: at baseline, just after finishing the eight week CR program, three months after program completion, and at three years after program completion. A bicycle exercise test is conducted at all four data collection points (Figure 1).

**Figure 1 Fig1:**
[figure not shown]
**Flowchart LC-REHAB study.** Cardiac rehabilitation (CR), Learning and Coping (LC).

Nine CR programs run continuously at the same time in all three hospitals. Eight of these programs are used for the study – four programs for the intervention (LC) arm and four programs for the control arm. The last program is used for patients who do not want to participate in the study. Patients are allocated consecutively to the eight programs which have continuous uptake and a maximum of twelve patients on each program.

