### Power calculations

From an existing CR database in RHWJ the standard deviation (sd) on the change in the SF-12 scales was known. It is expected that better coping ability could affect the scales ‘vitality’ (sd = 24.4 percentage points) and ‘mental health’ (sd = 13.4 percentage points). Necessary participant numbers were calculated under different assumptions which led us to choose a sample size of minimum 750 patients. If all patients complete the program, a difference in vitality of 5 percentage points and a difference in mental health of 2.75 percentage points will be detected with a power of 80% and a p-value of 0.05. With a dropout of 10 and 20% respectively, a difference in vitality of 5.3 and 5.6 respectively, and a difference in mental health of 2.9 and 3.1 respectively, will be found under the same assumptions.

From in vivo precision of DXA scans a sd of 0.187 in total body fat (TBF) at two consecutive measures was known [48]. We will include at least 150 patients to receive DXA scans in this study. Selection was based on the computer generated randomisation, thus every fourth participant was allocated for DXA scan – stratified for two hospital units, gender and diagnosis. If all 150 patients attend the DXA scan a difference of 0.09 kg in TBF will be able to be shown with a power of 80% and a p-value of 0.05.

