### Statistical methods

Data is entered into dedicated databases and statistical analysis will be performed using STATA13 [49]. Cleaning and data management will be carried out on all relevant datasets and all statistical analysis will be performed using the ‘intention to treat’ principle. Descriptive statistics will be used to describe baseline variables. Differences in change in mean scores from baseline to follow-up between the two groups for continuous variables will be tested using unpaired t-tests provided they are normally distributed. Non-parametric tests will be performed for non-normally distributed data. Multiple regression analysis will be undertaken to check for interactions between gender, age and socio-economic background. For dichotomous variables, chi-square tests or logistic regression will be performed. Readmissions and survival will be analysed using Cox regression analysis.

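### Care is delivered in group programs nested within arm, but the SF-12 power calculation and the named t-tests and chi-square tests treat patients as independent

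*Protocol article*

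**What the plan says.** Allocation is by individual: "The randomisation is computer generated in a 1:1 ratio", stratified by hospital unit, diagnosis and gender (Design).

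Delivery is by group. The text following Figure 1 assigns four programs to LC and four to control, and adds: "Patients are allocated consecutively to the eight programs which have continuous uptake and a maximum of twelve patients on each program". The Design section says of each arm that "patients are supported by the same team of nurse and physiotherapist throughout the eight week period". For LC, the Intervention group and Evaluation meetings sections go further: a nurse, a physiotherapist and an experienced patient are attached to a given program and run its sessions together. The Control group section confirms that standard rehabilitation is also given in groups.

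The Power calculations section takes the standard deviation of change for SF-12 vitality ("sd = 24.4 percentage points") and mental health ("sd = 13.4 percentage points"). The calculation led the authors to "choose a sample size of minimum 750 patients". With full completion, differences of 5 points (vitality) and 2.75 points (mental health) "will be detected with a power of 80% and a p-value of 0.05". Dropout is allowed for; correlation within groups is not.

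The Statistical methods section names unpaired t-tests for change in continuous outcomes, with non-parametric tests as the fallback. It continues: "For dichotomous variables, chi-square tests or logistic regression will be performed. Readmissions and survival will be analysed using Cox regression analysis". Program and team are not mentioned.

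**The concern.** Each program belongs wholly to one arm, so any difference between programs or teams feeds straight into the comparison of arms. Individual randomisation does not remove this, because the correlation arises after allocation, when patients are taught and trained together.

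The article's own rationale makes such correlation plausible. LC is meant to work through shared narratives, identification with peers and weekly adjustment of the teaching by the team. In the control arm, staff have no formal rehabilitation training and learned by observing sessions, so staff may differ there too.

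If the correlation exists and is ignored, a few unusually engaging groups count as many independent patients. P-values come out too small, confidence intervals too narrow, and the power statement too favourable. Adherence is exposed as well as SF-12: it is a primary outcome, measured as program completion and the share of planned sessions attended, and both are produced inside these groups.

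**Working it through.** **Inputs from the article.** N = 750, so 375 per arm at 1:1; SD of change 24.4 (vitality) and 13.4 (mental health); differences 5 and 2.75; power 80%; alpha 0.05 (sidedness is not stated, but two-sided reproduces the figures); at most 12 patients per program.

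**Assumed.** The ICC. The article gives none, so a range of 0.005 to 0.05 is shown.

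**Step 1: reproduce the plan's figures under independence.** n per arm = 2 × (1.96 + 0.8416)² × SD² / difference².

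- Vitality: 2 × 7.849 × 24.4² / 5² = 373.8, so 374 per arm and 748 in total. Power at 750 is 80.1%.
- Mental health: 2 × 7.849 × 13.4² / 2.75² = 372.7, so 373 per arm and 746 in total. Power at 750 is 80.2%.
- 10% dropout (675 patients): power 80.6% for 5.3 and 80.3% for 2.9.
- 20% dropout (600 patients): power 80.3% for 5.6 and 80.9% for 3.1.

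Every SF-12 figure reproduces with a design effect of 1. The total of 750 leaves almost no slack beyond the 748 and 746 required.

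**Step 2: allow for correlation within groups.**

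- Design effect: DE = 1 + (m − 1) × ICC, with m the group size.
- Standard error of the vitality difference: 24.4 × √(2 × DE / 375), which is 1.782 at DE = 1.
- Power: Φ(5 / SE − 1.96).
- Detectable difference at 80% power: 2.8016 × SE.
- Actual two-sided alpha of the unadjusted test: 2 × (1 − Φ(1.96 / √DE)).

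Worked case, m = 12 and ICC = 0.05: DE = 1 + 11 × 0.05 = 1.55. SE = 1.782 × √1.55 = 2.22. Power = Φ(2.25 − 1.96) = 61.6%. Detectable difference = 2.8016 × 2.22 = 6.22. Alpha = 2 × (1 − Φ(1.574)) = 11.5%.

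| Group size | ICC | DE | Actual alpha | Power for 5 vitality points | Detectable vitality difference |
|---|---|---|---|---|---|
| 12 | 0.005 | 1.055 | 5.6% | 78.0% | 5.13 |
| 12 | 0.01 | 1.11 | 6.3% | 75.9% | 5.26 |
| 12 | 0.02 | 1.22 | 7.6% | 71.9% | 5.51 |
| 12 | 0.05 | 1.55 | 11.5% | 61.6% | 6.22 |
| 6 | 0.005 | 1.025 | 5.3% | 79.1% | 5.05 |
| 6 | 0.01 | 1.05 | 5.6% | 78.2% | 5.12 |
| 6 | 0.02 | 1.10 | 6.2% | 76.3% | 5.24 |
| 6 | 0.05 | 1.25 | 8.0% | 70.9% | 5.58 |

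Mental health behaves the same way. With groups of 12, power for 2.75 points runs from 78.1% to 61.7% over this ICC range, and the detectable difference from 2.82 to 3.41.

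**Step 3: scale.** With groups of 12, an ICC of 0.01 raises the detectable vitality difference about as much as the 10% dropout that the plan does allow for (5.3). The two losses would add to each other.

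The formula assumes closed groups of equal size. Programs here fill on a rolling basis and 12 is a ceiling, so the table is an approximation.

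**The case against.** The strongest reply is that the harm depends on a quantity the article does not give. At an ICC of 0.005 with groups of 12, power is still 78%, and with groups of 6 it is 79%, which is a negligible loss. This stands: the omission is certain, its size is not.

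Four stronger readings are tempting and are not supported.

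- *Correlation persists within each program slot for the whole of recruitment.* The effective clusters would then be few and very large and the loss far greater. The text ties the team to an eight-week period and does not say that one team keeps one program for years. Lasting differences due to hospital are balanced by the stratified randomisation, and a t-test that ignores this stratification is, if anything, slightly conservative for that component.
- *Every control program has its own team.* Teams attached to a program are explicit for LC only. For control, the article says only that the team stays with the patients.
- *All planned tests ignore clustering.* Logistic and Cox regression are named without a variance estimator, and a fuller analysis plan could add random effects, frailty or cluster-robust errors. Only the t-tests and chi-square tests are clearly fixed, and chi-square is listed as an alternative to logistic regression.
- *The primary outcomes are shown to be underpowered.* The 80% figure concerns SF-12 scales, which the Outcomes section lists as secondary. The Power calculations section states no power for adherence, morbidity or mortality.

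The objection does not remove the mismatch. Delivery is grouped within arm, the power figures hold only at a design effect of 1, and two of the named tests cannot carry a program or team term. An unseen analysis plan could correct this only by departing from tests that the article names.

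**Conclusion.** The point holds in conditional form. If outcomes correlate within program or team, the named t-tests and chi-square tests give standard errors that are too small, and 750 patients do not give the stated 80% power for the SF-12 scales. With groups of 12 and an assumed ICC of 0.005 to 0.05, the unadjusted standard error is too small by a factor of about 1.03 to 1.25 (√1.055 to √1.55); alpha, power and detectable differences move as in the table.

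Confidence is high for the omission and its direction, and limited for its size, which rests on the assumed ICC and on treating rolling groups as closed ones. For adherence the same direction applies to any t-test or chi-square test, but the article gives no figures from which to size it.

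**What to change.** 1. **Define the cluster and record it.** State whether it is the program, the team or both, in a way that suits rolling entry. Fixed intake cohorts do not exist here, so the definition might use the program together with the team in charge during the patient's eight weeks. Record it for every patient; the article describes allocation to programs but does not say that program or team is kept in the dataset.
2. **Continuous outcomes**, including SF-12 change and the share of sessions attended: replace the unpaired t-test with a linear mixed model that has a program/team random effect and a small-sample degrees-of-freedom correction such as Kenward-Roger. Check that the software version named in the article offers it. This correction belongs to the linear mixed model and does not carry over to the models in item 3.
3. **Completion, readmission and survival:** use logistic and Cox models that account for program/team, through a random effect or frailty, or cluster-robust errors suited to few clusters. Drop the chi-square test as the main analysis of completion.
4. **Restate the detectable SF-12 differences** over a stated ICC range, as in the table, combined with the dropout scenarios.

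The cost is analysis text, code and one recorded variable per patient. The intervals will be wider and the stated power less favourable. Keeping 80% power for 5 vitality points with groups of 12 would need 750 × DE patients: 792 at an ICC of 0.005 and 1,163 at 0.05. If recruitment stays at 750, the larger detectable difference should simply be reported. The change should be fixed before outcome data are analysed.

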### Participants

Recruitment was initiated on 30^th^ of November 2010. Inclusion criteria are: patients aged 18 years and above discharged from hospital with either IHD (ICD-10 codes: I20 and I21) or HF (ICD-10 codes: I50.0-3, I50.8, I50.9, I42.0, I42.6-9, I11.0, I13.0 and I13.2), assigned and motivated for CR. Exclusion criteria are: Acute coronary syndrome less than five days before randomisation, active peri- myo- or endocarditis, symptomatic and untreated valve disease, severe hypertension with blood pressure >200/110 mmHg, other severe cardiac or extra cardiac disease, planned revascularisation, senile dementia, assessed as having low compliance, or former participation in the study.

### Recruitment/settings

Study information is sent by mail to eligible patients and they are informed of the study via telephone by this paper’s first author. Informed consent is obtained one to two weeks after discharge by health professionals working in the CR units; either a nurse or a physiotherapist.

All CR programs start the first working day after randomisation and are performed in the CR units at each of the three hospitals. The majority of measurements are taken by health professionals or via questionnaires. Laboratory testing is performed at the hospitals’ laboratories, and DXA scans are performed at the Department of Nuclear Medicine within two of the three hospitals.

### Group allocation

#### Intervention group

CR programs with incorporated LC strategies start with an individual clarifying interview followed by an eight week group based training and education period and finish with another individual clarifying interview. Experienced patients participate as co-educators in all of the education sessions and in one of the training sessions each week. Each week, an hour long evaluation meeting is conducted by the team of nurse, physiotherapist and experienced patient who are assigned to the specific program.

The LC health professionals - nurses and physiotherapists - have completed a competence-education course in LC strategies lasting eight days with the experienced patients participating in the last four. Public Health and Quality Improvement, Central Denmark Region, Aarhus, Denmark conducts this course containing lectures, group work and supervision. An outline of this course can be obtained from the author. Experienced patients were recruited from participants in previous CR programs. The experienced patients are clinically stable and have a high level of coping with their disease. The latter was determined by this paper’s first author during interview, based on her experience as a cardiology nurse and her knowledge of LC strategies. LC strategies take a situated, reflexive and inductive approach to education, by focusing on the individual patients’ needs and concerns in relation to the present topic rather than following a structured, pre-written slide show. Materials are developed for each topic including background literature and questions designed to facilitate discussion among patients.

